#### Serum retinol analyses

The effect of vitamin A supplementation on vitamin A status will be assessed on a sub-sample of infants at 2 weeks (to establish whether there has been a short term improvement in vitamin A status) and 3 months (to establish whether there has been a longer term improvement in vitamin A status). Mean serum vitamin A and retinol binding protein concentrations at each site will be compared in the vitamin A and placebo groups using independent sample t-tests for the overall sample. If the distributions are found to be skewed, the mean log concentrations will be compared. Further analyses will be conducted in which retinol levels will be adjusted for CRP, which is a biochemical marker of infection. Maternal serum retinol concentrations will be analysed to assess the prevalence of maternal vitamin A deficiency.

#### Interim analyses by the DSMB

A common DSMB has been set up to monitor the progress of the three trials. The DSMB is responsible for monitoring and assessing the safety of the trial and consists of an epidemiologist, a statistician and a clinician/social scientist from each of the three study sites. It meets every six months, and all three trials are discussed at the same meeting. The DSMB examines adverse events and deaths within 3 days of supplementation every 3 months. In addition, there will be two formal interim analyses of mortality to six months for each site. The first interim analysis will take place when approximately one third of participants have reached six months of age and the second interim analysis will take place when approximately half of the participants have reached that point.

The analysis by DSMB is conducted in a blinded manner (treatment groups X and Y). The randomization code will be broken if there is clear evidence of a difference in mortality between the two arms. A trial will be stopped if there is early evidence of a significantly lower mortality in the vitamin A group compared with placebo according to P values specified in the O'Brien- Fleming rules [30]. For the first interim analysis, a P value of < 0.001 is specified; for the second, the specified P value is < 0.015. Only the trial centre showing increased or decreased mortality with these specified p values will be stopped; the other trial centre/s will continue until the next interim analysis or the final analysis as appropriate. For the final analysis for each site, an increase or decrease in mortality in either group will be considered significant if the P value is < 0.047; this lower value is specified to account for the fact that the data will have been examined twice before the final analysis [30].

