### Sample size

The infant mortality rate was estimated to be about 50 per 1000 live births in India and about 60 per 1000 in Ghana and Tanzania. Assuming a 10% loss to follow up, sample sizes at each site were calculated to detect a 15% reduction in mortality from enrolment to 6 months of age, which is the primary outcome, with 85% power and a 5% significance level. The required sample size was 40,200 in India and 32,000 each in Ghana and Tanzania.

This sample size would also be enough to detect a difference of 15% in post-enrolment infant mortality and 20% in post-enrolment neonatal mortality (secondary outcomes).

Blood samples are requested from 720 randomly selected infants at 2 weeks of age and another 720 randomly selected infants and their mothers at 3 months of age at each site. This sample size is sufficient to detect an increase of 0.25 standard deviation (SD) in mean serum retinol in the intervention group after supplementation, with 80% power in each site, and assuming that about 30% families will refuse to allow collection of blood samples.

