### Ethical issues

Communities in all sites were sensitized to the study prior to randomization. This was achieved through meetings with community leaders and with community groups. Informed written consent is obtained from one of the parents for each neonate before he/she is enrolled in the study. Any death within 72 hours of supplement administration, irrespective of the cause and relationship with supplementation, is communicated to WHO by the site investigators within 10 days of the team member becoming aware of the event. WHO communicates this information to the Data Safety Monitoring Board (DSMB). The DSMB reviews this information every 3 months, and all the collected data every six months to determine if the study should be continued or stopped, based on pre-decided stopping rules.

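### The O'Brien-Fleming thresholds do not fit looks at one third and one half, and the final 0.047 does not fully pay for them: type I error is up to 5.5% on a two-sided reading

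*Protocol article*

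**What the plan says.** Sample size sets each trial up "with 85% power and a 5% significance level". Interim analyses by the DSMB then fixes the monitoring plan for mortality to six months, site by site:

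- Timing, look 1: "The first interim analysis will take place when approximately one third of participants have reached six months of age".
- Timing, look 2: "the second interim analysis will take place when approximately half of the participants have reached that point".
- Source of the thresholds: "according to P values specified in the O'Brien- Fleming rules".
- Interim thresholds: "For the first interim analysis, a P value of < 0.001 is specified; for the second, the specified P value is < 0.015".
- Final analysis: a difference in either direction "will be considered significant if the P value is < 0.047; this lower value is specified to account for the fact" of two earlier examinations.

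On direction the section says two things. One sentence provides for stopping only when mortality is significantly lower with vitamin A. A later one reads: "Only the trial centre showing increased or decreased mortality with these specified p values will be stopped".

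**The concern.** An O'Brien-Fleming boundary depends on when the looks occur. The stated values resemble the familiar set for three equally spaced looks, with the second at two thirds, but the plan puts the second look at one half. A threshold of 0.015 there spends more alpha than the named rule would, and the final 0.047 may then be too generous to hold 5%.

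Two things are at stake. A site's final claim of significance would be slightly anti-conservative. A site could also stop at its second look on weaker evidence than the cited rule requires. Each site is tested and can be stopped on its own, and the Discussion expects these trials to inform policy for or against the intervention.

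**Working it through.** **Inputs.** Two-sided P values 0.001, 0.015 and 0.047 correspond to |Z| = 3.291, 2.432 and 1.986. Look times are t = 1/3, 1/2, 1. The target is 5%, taken as two-sided because the final test counts a difference in either direction.

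**Step 1: do the thresholds have the O'Brien-Fleming shape?** That rule keeps Z × √t constant across looks.

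| Second look at | Look 1 | Look 2 | Final |
|---|---|---|---|
| 1/2 (as planned) | 3.291 × √(1/3) = 1.900 | 2.432 × √(1/2) = 1.720 | 1.986 |
| 2/3 | 1.900 | 2.432 × √(2/3) = 1.986 | 1.986 |

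At one half the second value is out of line. At two thirds it equals the final value, so 0.015 belongs to a look at about two thirds.

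**Step 2: what does the rule give?** Solving for the constant that yields exactly 5% two-sided:

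- Classical O'Brien-Fleming at 1/3, 1/2, 1: constant 1.979, nominal P 0.0006 / 0.0051 / 0.0479.
- Classical O'Brien-Fleming at 1/3, 2/3, 1: constant 2.004, nominal P 0.0005 / 0.0141 / 0.0451.
- Lan-DeMets O'Brien-Fleming-type spending at 1/3, 1/2, 1: 0.0007 / 0.0053 / 0.0477, or 0.0002 / 0.0030 / 0.0490 with 0.025 spent per side.

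No form tried gives 0.015 at half information.

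**Step 3: error of the plan as written.** The null probability of first crossing at each look, by recursive numerical integration of the joint distribution of the test statistics, two-sided at 1/3, 1/2, 1, is

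0.0010 + 0.0142 + 0.0398 = 0.0550.

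A simulation of 8 million runs gave 0.0549. Alpha spent by the second look is 0.0010 + 0.0142 = 0.0152, against about 0.005 under O'Brien-Fleming at those times.

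**Step 4: sensitivity to what the section leaves open.** The fractions 0.40/0.55 and 0.50/0.67 are assumptions, because the article does not give the age distribution of deaths.

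| Information at looks 1, 2 | Two-sided stopping: total | Benefit-only interim stopping: total | of which benefit direction (nominal 2.5%) |
|---|---|---|---|
| 1/3, 1/2 | 5.50% | 5.10% | 2.75% |
| 0.40, 0.55 | 5.41% | 5.06% | 2.71% |
| 0.50, 0.67 | 5.21% | 4.95% | 2.60% |

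Even if the second look were at two thirds (1/3, 2/3), the stated set gives 5.24% two-sided, because each of its values is slightly above the exact O'Brien-Fleming one.

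**Step 5: final threshold that restores 5%.** With 0.001 and 0.015 kept and two-sided stopping, it is 0.0416 at 1/3, 1/2 and 0.0447 at 0.50, 0.67.

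**The case against.** The strongest reply is that 5.5% depends on two readings the text does not force.

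*Information.* The primary analysis is Cox regression on person time (General principles for analysis; Main effects), where information is counted in deaths. The looks are triggered by infants reaching six months, but younger enrolled infants may already have contributed deaths, so the information fractions may exceed one third and one half. At an assumed 0.50 and 0.67, O'Brien-Fleming gives 0.0044 / 0.0140 / 0.0443. There 0.015 is close to the rule and 0.001 is stricter than it. This stands: calling 0.015 about three times too lenient holds only if information equals the participant fraction.

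*Direction.* If interim stopping is for benefit only, the total falls to about 5.0-5.1%. This stands too, but the benefit tail remains above 2.5%, and the section's other sentence supports the two-sided reading.

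A reader might also infer extra looks from Ethical issues, which has the board review "all the collected data every six months to determine if the study should be continued or stopped, based on pre-decided stopping rules". The text does not support that. The interim section describes the two formal mortality analyses as additional to the six-monthly meetings, and ties the P values only to those two analyses and the final one. No efficacy test is prescribed at the other reviews, so they add nothing to the error computed here.

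**Conclusion.** The point holds in a limited form. At the look times written in the section, 0.015 is not an O'Brien-Fleming value, and on every two-sided reading examined the stated set exceeds 5%. The final 0.047 therefore does not fully account for the two looks, as the section says it does.

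The size is 5.50% when stopping is two-sided and information equals the participant fraction, and 5.2-5.4% on the assumed death-based fractions. With benefit-only interim stopping the total is near nominal and the excess is confined to the benefit tail.

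It would be tempting to state flatly that each trial runs at 5.5%. The documents do not support that, because 5.5% is the upper end of a range that depends on a direction the section leaves contradictory and an information scale it does not define. The inflation is modest, but it comes from figures the article fixes itself.

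**What to change.** 1. Reconcile the two sentences on direction in Interim analyses by the DSMB, so that it is clear whether the interim P values apply to lower mortality only or to both directions. Any boundary for increased mortality is for the sponsor and the DSMB to set. Replacing 0.015 by a smaller fixed number for both directions would also make stopping for increased mortality harder, so a simple substitution is not recommended.
2. Define information as deaths in the primary analysis, and state whether deaths in infants not yet six months old count at an interim look.
3. Compute the efficacy boundaries and the final threshold with a Lan-DeMets O'Brien-Fleming-type spending function at the observed information fractions. This also handles looks that are only approximately timed.
4. If 0.001 and 0.015 are kept, lower the final threshold from 0.047 to about 0.042 (0.0416 at 1/3, 1/2; 0.0447 would do at 0.50, 0.67).

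The cost is an amendment to one section and a slightly stricter final threshold.

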### Timelines

Enrolment of participants started between June and August 2010 in the three studies and is likely to be completed by September 2012. After enrolment is completed, follow up visits will continue to be conducted for a period of 6 months. This will ensure that all enrolled infants have a chance to complete their 6 month follow up. A proportion of enrolled infants will therefore have less than 12 months follow up.

## Discussion

The three ongoing studies described in this paper are the largest studies evaluating neonatal vitamin A and are expected to provide definitive information to help in formulating policy in favour of or against this intervention. All studies are individually randomized, double blind placebo controlled trials. Each is individually powered to detect a moderate but important effect on mortality in enrolled infants.

The studies are being conducted in Ghana, Tanzania and India and combined with previous studies (conducted in Indonesia, Bangladesh, Nepal, India, Guinea-Bissau and Zimbabwe), will provide information generalizable to Africa and South Asia. There are very few exclusion criteria because the studies are expected to answer a pragmatic question about the effect of routine use of neonatal vitamin A.

The intervention is a single dose of 50,000 international units within the first three days of life, consistent with the previous studies that have tested this intervention. The comparison is placebo with blinding achieved through numbered supplements. This is the most robust design available to ascertain efficacy of an intervention.

The primary outcome for this study was chosen to be mortality in the period from supplementation to 6 months of age. This was done because there is a policy on vitamin A supplementation in the second half of infancy in many developing countries, and the effects of the intervention (neonatal vitamin A supplementation) will be changed by this large supplement provided in the second half of infancy. However, two previous studies from Guinea-Bissau have suggested that the intervention may have a negative effect in the second half of infancy. Therefore, we have added mortality from supplementation until 12 months of age as a secondary outcome in consultation with the DSMB of the study.

We have several subgroup analysis decided *a priori*. These subgroup analyses are planned to confirm or refute hypotheses raised by previous studies and systematic reviews. A pooled analysis of two studies from Guinea-Bissau raised the hypothesis that the intervention may have a negative effect in girls, but a meta-analysis of all available trials did not find this interaction. The studies from Guinea-Bissau have also raised the hypothesis that effects may be different before or after the first dose of DTP immunization. A meta-analysis hypothesized that the effects may be different in low or normal birth weight infants and by the level of vitamin A deficiency in populations.

The biological rationale for the potential effect of neonatal vitamin A is not known. It has been hypothesized that the intervention could work through positively affecting the immune system or by promoting the maturation and integrity of the epithelium. A set of parallel animal and human studies is being conducted to understand the transport and metabolism of the neonatal vitamin A dose and its effects on the innate and adaptive immune system. These studies will shed more light on the potential biological mechanisms through which this intervention may work.

However, policy formulation will largely be based on the results of efficacy of the intervention from the ongoing randomized controlled trials. These results will be combined with results of previous studies in a new meta-analysis for an overall effect. The data from the three new studies, as well as previous studies if possible, will be pooled to carefully examine subgroup effects.

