#### India

##### Study setting

The study is being conducted in rural sites of Faridabad and Palwal districts, in the state of Haryana, India. The population of the two districts is ~2.1 million. Based on data obtained from a previous trial in the area, the birth rate in this population is 25 per thousand, the infant mortality 60 per thousand live-births per year and the less than six month mortality rate is 50 per thousand live-births per year.

The HIV prevalence among women attending antenatal care in Haryana in the year 2006 was estimated to be 0.13% [22]. Vitamin A deficiency is likely to be a problem in mothers and young children. The prevalence of subclinical vitamin A deficiency based on serum retinol < 20 μg/dl in children aged 3 to 6 years was recently reported as 14.2% [23]. Prevalence of signs and symptoms of vitamin A deficiency among children 5 to 9 years and 10 to 14 years in Haryana was reported to be 15 and 25 per thousand respectively [24]. During the study implementation period there are no programs or research on micronutrients or maternal vitamin A supplementation ongoing in the area. The national program recommends 6 monthly doses of vitamin A (100,000 IU) starting at 9 months of age; the percentage of children 12-35 months of age given vitamin A in the last 6 months in Haryana was 15.9% [25]. In the study areas, around half the families are nuclear; the median number of family members is 6 (5, 8). Around half (52%) of mothers of young children have never been to school; 95% of women do not work outside home. The median (range) family income per year in Year 2010 was Indian Rupees 36,000 (600 to 4600000). The most common sources for seeking care for ill children are private practitioners within and outside of the villages (~ 60%). Over half the deliveries are conducted at home by traditional birth attendants and over 35% of infants are born low birth weight (< 2500 g). Around 40% of under twos have < -2 HAZ and 17% have WHZ score < -2 [26].

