### Analysis plan for the three studies

#### Definitions

The primary outcome of the study is defined as a death between supplementation and 180 days of life (6 months). Secondary mortality outcomes are defined as a death between supplementation and 28 days of life, and a death between supplementation and 365 days of life. Severe morbidity is defined as one or more hospitalizations due to any illness between supplementation and day 180 of life. A hospitalization is defined as an admission to hospital as an inpatient, as reported by the mother. Infants will only contribute one hospitalization episode to the analysis, regardless of how many times they were hospitalized in the first six months of life.

Potential adverse events are defined as specific events occurring within 3 days of supplementation. These events include all deaths within 3 days of supplementation; bulging fontanelle confirmed by the research team through a physical examination of the infant; or primary caregiver reports of fever, vomiting, diarrhoea, inability to suck or feed, or convulsions in the first 3 days post supplementation.

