#### Main effects

For the primary outcome, all-cause mortality between supplementation and 180 days of age, data will first be analysed using person time, i.e. infant years of follow up, as the denominator. Hazard ratios and 95% confidence intervals comparing the effect of vitamin A on deaths in the first half of infancy between vitamin A and placebo groups will be calculated using Cox regression. In the unlikely event that there is imbalance between the treatment and control groups, the final statistical models will include adjustment for all imbalanced variables. The effect of vitamin A supplementation on all-cause mortality between supplementation and 180 days of age will also be assessed using enrolled infants as the denominator. The principles outlined above will be followed, and logistic regression will be used to compare mortality in the vitamin A and placebo arms.

The effect of vitamin A supplementation on secondary outcomes (all-cause mortality from supplementation to 12 months, all-cause mortality from supplementation to end of the neonatal period, hospitalizations) will be assessed using similar methods to the primary analysis; both person time and enrolled infants will be used as denominators for all analyses.

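### The 12-month outcome was added because of suspected harm at 6 to 12 months, but it counts deaths from dosing and so has little power to detect that harm

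*Protocol article*

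**What the plan says.** The Discussion explains why the primary outcome stops at six months and then raises a safety signal: "two previous studies from Guinea-Bissau have suggested that the intervention may have a negative effect in the second half of infancy". Its response follows directly: "Therefore, we have added mortality from supplementation until 12 months of age as a secondary outcome".

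The Definitions section fixes this outcome as "a death between supplementation and 365 days of life", so the clock starts at dosing. The secondary objectives use the same window. Main effects lists the secondary outcomes as "all-cause mortality from supplementation to 12 months, all-cause mortality from supplementation to end of the neonatal period, hospitalizations", analysed like the primary outcome (Cox regression on person-time, and logistic regression on enrolled infants). No overall comparison restricted to the second half of infancy appears there. A 6 to 12 month window appears only in the opening line of Sub-group analyses, for effects by birth weight, sex, DTP timing, wealth and maternal supplementation.

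For India, Study setting gives "the infant mortality 60 per thousand live-births per year and the less than six month mortality rate is 50 per thousand live-births per year".

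**The concern.** The stated worry is about one period, and the outcome adopted in response covers two. Most deaths in the combined window come before the period of concern, so a late effect is diluted by the early one. If the early effect is a benefit, which is the trial's primary hypothesis, it offsets the late effect further.

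These trials are meant to settle policy. A 12-month ratio near 1 could be taken as evidence against the late-harm signal when the comparison had little chance of revealing it.

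**Working it through.** **Inputs from the protocol article**
- India: 40,200 infants, so 20,100 per arm. With 10% loss, 20,100 × 0.90 = 18,090 followed per arm.
- Ghana and Tanzania: 32,000 each, so 16,000 × 0.90 = 14,400 per arm.
- Target: "detect a 15% reduction in mortality from enrolment to 6 months of age", so the early ratio is 0.85.
- India, deaths before six months: 50/60 = 83%. Deaths at 6 to 12 months: 60 − 50 = 10 per 1000.

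**Placebo risk to six months.** This is not stated and had to be inferred. Sample size says "The infant mortality rate was estimated to be about 50 per 1000 live births in India and about 60 per 1000 in Ghana and Tanzania", which for India disagrees with the 60 per 1000 in Study setting. Taking the Sample size figures and subtracting the 10 per 1000 late deaths gives 40 per 1000 (India) and 50 per 1000 (Ghana, Tanzania). A two-proportion calculation (two-sided 5%, 85% power, ratio 0.85, continuity correction, divided by 0.90) then gives 40,229 and 31,880, against the stated 40,200 and 32,000. Using 50 and 60 per 1000 as the six-month risks gives about 31,300 and 25,800 without continuity correction, which does not match. So 40 then 10 per 1000 is a reasonable reading for India, with an early share of 40/50 = 80%.

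**Formulas**
- Cumulative ratio = (40 × early HR + 10 × late HR) / 50
- SE(log ratio) = √(1/d1 + 1/d0), where d1 and d0 are the deaths per arm
- Chance of significant harm = Φ(log ratio / SE − 1.96)

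**India, early 1.0, late 1.30**
- Cumulative: (40 + 13)/50 = 1.06. Deaths are 904.5 on placebo and 958.8 on vitamin A, SE 0.0464, so the chance is Φ(0.0583/0.0464 − 1.96) ≈ 24%.
- Direct, 6 to 12 months: 180.9 against 235.2 deaths, SE 0.0989, so Φ(0.2624/0.0989 − 1.96) ≈ 76%.

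**India, early 0.85**

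| Late HR | Cumulative ratio (95% CI) | Chance of significant harm, cumulative | Power, direct 6 to 12 months |
|---|---|---|---|
| 1.20 | 0.92 (0.84–1.01) | <1% | 44% |
| 1.30 | 0.94 (0.86–1.03) | <1% | 76% |
| 1.50 | 0.98 (0.89–1.07) | <1% | 99% |

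The cumulative ratio reaches 1.00 only when the late HR is (1 − 0.80 × 0.85)/0.20 = 1.60.

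**Truncated follow-up.** Timelines has visits ending six months after enrolment closes. With even enrolment over about 26 months, 6/26 = 23% of infants lack complete 12-month follow-up and lose on average half the late window, about 11.5% of late events. Removing 11.5% to 23% of late events lowers direct power at HR 1.30 to 70% and 64%. The cumulative figure with no early effect falls too, from 24% to 20% and 17%.

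**Ghana and Tanzania (14,400 per arm; assumed 40/10, 50/10 or 40/15 per 1000).** For late HR 1.30 and no early effect, cumulative power is 18 to 36% and direct power 66 to 83%, before truncation. At late HR 1.20 and 10 per 1000, direct power is about 37%.

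**Sensitivity to the early share.** The 83% is per live birth and includes deaths before dosing. With an assumed early share of about 70% (India 25/10, Ghana or Tanzania 35/15 per 1000), early 0.85 then late 1.50 gives a cumulative ratio of about 1.04 and a 9 to 14% chance of showing harm. That is more than 1%, but far below the direct comparison.

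**The case against.** **The cumulative outcome is legitimate.** It compares the arms as randomised and asks whether more infants are alive at 12 months. The Discussion can be read as asking that net question and does not say the outcome is meant to isolate late harm. This stands. A reader might infer that a ratio of 0.94 would wrongly present harm as benefit. It would not: with an early ratio of 0.85 and a late one of 1.30, fewer vitamin A infants have died by 12 months, and 0.94 reports that correctly. It also needs a real early benefit. Without one, late harm is diluted but keeps its direction.

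**The article is condensed.** A reader might infer that no overall 6 to 12 month estimate exists anywhere in the plan. The full protocol and analysis plan are not shown, so that cannot be claimed. The point rests on what is stated: a reason, an outcome offered in response, and a mismatch between them.

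**Sub-group analyses names the 6 to 12 month window.** Sex strata cover all infants, so taken literally some late results would be presented. But these are effects by subgroup, subgroup hazard ratios are tied to an interaction p-value below 0.01, and the window matches neither mortality outcome in Definitions. It does not supply an overall contrast.

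**Both windows are reported.** A shift from 0.85 to 0.94 would be visible, and late deaths per arm could largely be found by subtraction. This reduces the masking. It still leaves the late estimate, its interval and its test to be built after the results are known.

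**Non-proportional hazards.** The programme supplement is a weak argument in India, where it starts at nine months with 15.9% coverage, and the logistic analysis does not need proportionality. This stands, and the point does not depend on it.

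**Conclusion.** The point holds as a cheap improvement. "all-cause mortality from supplementation to 12 months" is a valid net outcome that is poorly suited to detecting the late harm given as the reason for adding it. In India, at a late hazard ratio of 1.30 with no early effect, it has about a third of the power of a direct comparison. With the targeted early benefit it has almost none.

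The late hazard ratios are illustrative and do not come from the documents. The 40/10 split is inferred from the sample size, and only India gives a split at six months. The under-1% figure depends on that split; the loss of power relative to a direct comparison appears in every case examined.

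The documents do not support the stronger reading that the trials would declare vitamin A safe to 12 months; no such conclusion is planned in the text.

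**What to change.** In Main effects, pre-specify a Cox model with follow-up split at day 180. Report the overall vitamin A versus placebo hazard ratio with its 95% interval for supplementation to day 180 and for days 181 to 365, with a treatment-by-period test. Keep supplementation to day 365 as the net summary. State that any conclusion on late harm rests on the 181 to 365 day estimate. Reconcile the 6 to 12 month window in Sub-group analyses with Definitions at the same time.

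The cost is a few lines of text and one model on data already being collected to 12 months. Recruitment, visits and the primary analysis do not change. The downside is one more secondary estimate, conditional on survival to day 180, to be read beside the cumulative one. Its power for small harms is limited (about 37 to 44% at a ratio of 1.2, before truncation), so a null late result should be reported by its interval and not as absence of harm.
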